## Abstract

**Background:**

Individuals with heterozygous familial hypercholesterolemia (heFH) have higher levels of low-density lipoprotein cholesterol (LDL-C) and are predisposed to premature cardiovascular disease. Alirocumab is a fully-human, monoclonal antibody targeted to proprotein convertase subtilisin/kexin type 9 currently in Phase 3 development for the treatment of hypercholesterolemia. Described here are three ODYSSEY Phase 3 trials, FH I (NCT01623115), FH II (NCT01709500) and HIGH FH (patients with heFH and LDL-C levels ≥160 mg/dL) (NCT01617655), in which alirocumab is further evaluated in the heFH population.

**Methods:**

Multicenter, multinational, randomized, double-blind, placebo-controlled studies have been designed to evaluate efficacy and safety of alirocumab in more than 800 patients with heFH who are not adequately controlled with a maximally-tolerated stable daily dose of statin for ≥4 weeks prior to the screening visit, with or without other lipid-lowering therapy. Patients are randomized (2:1) to receive alirocumab or placebo via a 1-mL subcutaneous auto-injection every 2 weeks (Q2W) for 78 weeks. In studies FH I and II, if their Week 8 LDL-C level is ≥70 mg/dL, patients will undergo a dose uptitration from 75 to 150 mg alirocumab Q2W at Week 12. In HIGH FH, patients will receive alirocumab 150 mg Q2W throughout the entire treatment period. The primary efficacy endpoint in all three studies is the percent change in calculated LDL-C from baseline to Week 24.

**Conclusions:**

The ODYSSEY FH studies are three Phase 3 studies aiming to further evaluate the efficacy and long-term safety of alirocumab as an effective therapeutic option for patients with heFH.

## Introduction

Heterozygous familial hypercholesterolemia (heFH) is a hereditary lipid metabolism disorder that predisposes affected individuals to cardiovascular (CV) disease [1]. Patients with heFH typically have very high low-density lipoprotein cholesterol (LDL-C) levels—often >190 mg/dL at the time of diagnosis—that are associated with high risk for premature CV disease [2, 3]. However, a recent consensus statement highlights that in most countries less than 1 % of patients with heFH are, in fact, diagnosed [4].

Findings from observational studies have shown that the risk of coronary heart disease (CHD) is reduced in heFH patients receiving statin therapy [5–7]; however, even with this treatment, the risk of CHD is still greater in heFH patients than in the general population [5]. Despite the availability of lipid-lowering therapy (LLT), approximately 80 % of patients with heFH do not reach the recommended levels of LDL-C [8–12]. Given the increased CV risk in the heFH population, there is a need to provide patients with additional and more intensive lipid-lowering therapy [4, 13].

Proprotein convertase subtilisin/kexin type 9 (PCSK9), a therapeutic target currently under investigation, binds to LDL-C receptors, resulting in their degradation so that fewer receptors are available on liver cells to remove excess LDL-C from the plasma [14–17].

PCSK9 inhibition has the potential to provide a complementary mechanism to other LLTs to significantly reduce LDL-C beyond the efficacy of statins [15, 17–25]. Alirocumab (formerly REGN727/SAR236553; Sanofi-Regeneron) is a fully human, monoclonal antibody targeted to PCSK9 currently in Phase 3 development for the treatment of hypercholesterolemia.

In Phase 2 trials, alirocumab demonstrated significant reductions in LDL-C levels in patients receiving concomitant statin or statin plus ezetimibe therapy [NCT01288443; NCT01266876; NCT01288469; 21, 23, 24]. In these studies, alirocumab significantly (*p* < 0.001) reduced mean LDL-C levels by up to 72.4 %, and also showed favorable trends in other atherogenic lipid parameters including lipoprotein(a) [Lp(a)], triglycerides, non-high-density lipoprotein cholesterol (non-HDL-C), apolipoprotein (Apo) B, and anti-atherogenic fractions HDL-C and Apo A1. Specifically, a Phase 2 trial demonstrated that alirocumab reduced mean LDL-C levels by up to 67.9 % (*p* < 0.0001) in patients with heFH [24]. No dose-limiting adverse events (AEs) were identified in the Phase 2 studies [21, 23, 24], with the most common treatment-emergent AE (TEAE) in patients receiving alirocumab being mild injection site reaction. Five serious AEs (SAEs) occurred in four patients (1.5 %) who received alirocumab and two SAEs occurred in two patients (2.6 %) who received placebo.

The ODYSSEY Phase 3 alirocumab clinical trial program is designed to further assess the efficacy and safety of alirocumab in a range of clinical settings. The trials within the program evaluate a treat-to-goal approach, using a flexible dosing strategy for individualized therapy based on degree of LDL-C lowering required to achieve an adequate treatment response. This approach is designed to address patient populations unable to achieve desired LDL-C levels with the current standard of care. The program comprises a total of 14 studies planned to include more than 23,500 patients in over 2,000 study centers worldwide. Of these studies, the ODYSSEY program also includes a large cardiovascular outcomes trial evaluating the long-term impact of alirocumab and lower levels of LDL-C on the occurrence of cardiovascular events in 18,000 patients after a recent (<52 weeks) acute coronary syndrome event, with a randomized treatment period of 64 months. The aim of the ODYSSEY FH studies is to assess the efficacy and safety of alirocumab in patients with heFH who, despite their maximally-tolerated statin dose, with or without other LLT, continue to have suboptimal LDL-C levels and require additional pharmacologic management.

## Methods

### Study Design

All three Phase 3 ODYSSEY FH clinical trials are multicenter, multinational, randomized, double-blind, placebo-controlled studies designed to evaluate the efficacy and safety of alirocumab in patients with heFH not adequately controlled with their current LLT.

The FH I study (ClinicalTrials.gov identifier: NCT01623115) is being conducted at 89 sites across North America, Europe and South Africa, and has a planned population of 471 patients. The FH II study (ClinicalTrials.gov identifier: NCT01709500) is being conducted at 26 sites across Europe and has a planned population of 250 patients.

Both the FH I and II studies enroll heFH patients who have LDL-C levels ≥70 mg/dL at the screening visit and have a history of documented CVD, or heFH patients with LDL-C ≥100 mg/dL at the screening visit without a history of documented CVD (Fig. 1).

The HIGH FH study (ClinicalTrials.gov identifier: NCT01617655) is being conducted at 33 sites across North America, Europe and South Africa, and has a planned population of 105 patients with heFH and LDL-C levels ≥160 mg/dL at the screening visit (Fig. 1).

**Fig. 1 Fig1:**
[figure not shown]
Study designs. **a** ODYSSEY FH I, **b** ODYSSEY FH II and **c** ODYSSEY HIGH FH. *CV* cardiovascular, *heFH* heterozygous familial hypercholesterolemia, *LDL-C* low-density lipoprotein cholesterol, *LLT* lipid-lowering therapy, *NCEP ATP III TLC* National Cholesterol Education Program Adult Treatment Panel III Therapeutic Lifestyle Changes, *Q2W* every 2 weeks, *R* randomization, *SC* subcutaneous. ^a^At the end of the double-blind treatment period, patients will be offered the possibility to enter an open-label extension study, in which they will receive alirocumab. If patients opt out of entering the open-label treatment period, they will enter the 8-week follow-up period

The studies are being performed in accordance with the ethical principles that have their origin in the Declaration of Helsinki and all applicable amendments laid down by the World Medical Assemblies and the International Conference Harmonisation guidelines for Good Clinical Practice. Institutional review board or independent ethics committee approval of the protocols and informed consent forms were obtained from each study site, and written informed consent was obtained from all patients.

### Study Objectives

The primary efficacy objective in all three studies is to demonstrate the reduction of LDL-C by alirocumab, in comparison with placebo, as add-on therapy to stable, maximally tolerated daily statin therapy, with or without other LLT, after 24 weeks of treatment in patients with heFH. Secondary objectives common to all three studies include the evaluation of the effect of alirocumab in comparison with placebo on LDL-C after 12 weeks of treatment; the effect of alirocumab on other lipid parameters, e.g., Apo B, non-HDL-C, total cholesterol, Lp(a), HDL-C, triglycerides and Apo A1 levels; the long-term effect of alirocumab on LDL-C; the safety and tolerability of alirocumab; and evaluation of the development of anti-alirocumab antibodies.

### Inclusion Criteria

The principal inclusion criteria for all three studies are patients with heFH who are not adequately controlled with a maximally tolerated stable daily dose of statin for at least 4 weeks prior to the screening visit, with or without other LLT (Table 1).

**Table 1 Tab1:** Principal inclusion and exclusion criteria for ODYSSEY FH I, FH II, and HIGH FH

Principal inclusion criteria for all three studies	
Patients with heFH who are not adequately controlled^a^ with a maximally-tolerated stable daily dose of statin^b^ for at least 4 weeks prior to the screening visit, with or without other LLT	
Principal exclusion criteria	
Not on a stable dose of LLT (including statin) for at least 4 weeks and/or fenofibrate for at least 6 weeks, as applicable, prior to the screening visit or from screening to randomization	
Currently taking a statin that is not simvastatin, atorvastatin or rosuvastatin taken daily at a registered dose	
Receiving daily doses above atorvastatin 80 mg, rosuvastatin 40 mg or simvastatin 40 mg (except for patients on simvastatin 80 mg for more than 1 year, who are eligible)	
Use of fibrates, other than fenofibrate, within 6 weeks of the screening visit	
Fasting serum triglycerides >400 mg/dL (>4.52 mmol/L) at the screening visit	
Known history of homozygous FH	
FH I and II	HIGH FH
History of documented CVD and LDL-C <70 mg/dL (<1.81 mmol/L) at the screening visit Without history of documented CVD and LDL-C <100 mg/dL (<2.59 mmol/L) at the screening visit	LDL-C <160 mg/dL (<4.14 mmol/L) at the screening visit AND patient only on statin monotherapy without additional LLT

*CVD* cardiovascular disease, *FH* familial hypercholesterolemia, *heFH* heterozygous familial hypercholesterolemia, *LDL-C* low-density lipoprotein cholesterol, *LLT* lipid-lowering therapy, *MI* myocardial infarction

^a^FH I and II: not adequately controlled defined as an LDL-C ≥70 mg/dL at the screening visit in patients with a history of documented CVD OR LDL-C ≥100 mg/dL at the screening visit in patients without a history of documented CVD. HIGH FH: not adequately controlled defined as an LDL-C ≥160 mg/dL at the screening visit

^b^Maximally-tolerated statin dose defined as: the highest tolerable registered dose of daily statin currently administered to the patient, that is rosuvastatin 20 mg or 40 mg daily; atorvastatin 40 mg or 80 mg daily; simvastatin 80 mg daily (if already on this dose for >1 year). Patients who are not able to be on any of the above statin doses should be treated with the dose of daily atorvastatin, rosuvastatin, or simvastatin which is considered appropriate for the patient, according to the investigator’s judgment

The diagnosis of heFH must be made either by genotyping or clinical criteria. For those patients not genotyped, the clinical diagnosis may be based on either the Simon Broome criteria [26], meeting the criteria for definite FH, or the World Health Organization (WHO)/Dutch Lipid Network criteria [27] with a score of >8 points.

### Exclusion Criteria

The principal exclusion criteria for the FH I and II studies include patients with different LDL-C thresholds depending on their cardiovascular risk status: LDL-C <70 mg/dL (<1.81 mmol/L) in patients with history of documented CVD and LDL-C <100 mg/dL (<2.59 mmol/L) in patients without history of documented CVD.

The principal exclusion criterion for the HIGH FH study includes patients with an LDL-C level of <160 mg/dL (<4.14 mmol/L) at the screening visit (Table 1). Other key exclusion criteria common to the three studies are shown in Table 1.

### Study Procedures

The three FH studies consist of three periods: a screening period of up to 3 weeks, during which the patient or another designated person is trained to self-inject/inject study medication (1 mL administered via auto-injector); a 78-week double-blind treatment period; and an 8-week off-treatment follow-up period. It should be noted that, at the end of the 78-week treatment period in each study, patients will be offered the possibility to enter an open-label extension study, in which they will receive alirocumab. If patients opt out of entering the open-label treatment period, they will enter the 8-week follow-up period.

In FH I, FH II and HIGH FH, all eligible patients are randomized 2:1 to alirocumab or placebo. Randomization is stratified according to history of myocardial infarction (MI) or ischemic stroke for balance across study arms, intensity of statin treatment (atorvastatin 40 to 80 mg daily, or rosuvastatin 20 to 40 mg daily versus simvastatin irrespective of the daily dose, atorvastatin below 40 mg daily or rosuvastatin below 20 mg daily), and geographic region (where applicable).

At randomization, treatment kit numbers are allocated using a centralized treatment allocation system, which is either an interactive voice response system or an interactive web response system, depending on the site preference. Study patients, principal investigators and study site personnel remain blinded to all randomization assignments throughout the study. All lipid and anti-drug antibody results collected after randomization are masked.

In the three studies, the first auto-injection during the double-blind treatment period takes place at the site on the day of randomization (Week 0). Subsequent auto-injections are done by the patient or another designated person such as a spouse or relative at a patient-preferred location and occur every 2 weeks.

In FH I and FH II, patients randomized to alirocumab will receive a 75 mg 1 mL dose every 2 weeks (Q2W). Patients randomized to placebo will receive a 1 mL subcutaneous placebo injection in an identical auto-injector to maintain blinding. At Week 12, patients randomized to alirocumab undergo a dose uptitration to 150 mg Q2W, also given as a 1 mL auto-injection, if the Week 8 LDL­C level is ≥70 mg/dL (1.81 mmol/L). The continuation of the 75 mg dose or dose up-titration to the 150 mg dose will occur in an automated process without site or patient awareness.

In HIGH FH, at study entry, patients have an LDL-C level of ≥160 mg/dL (4.14 mmol/L) and they will be randomized to receive a 150-mg 1 mL dose of alirocumab or placebo-alirocumab, without the uptitration process, from randomization to the end of the 78-week double-blind treatment period.

During the three FH studies, all patients are asked to follow a stable, National Cholesterol Education Program Adult Treatment Panel III Therapeutic Lifestyle Changes diet or equivalent throughout the entire study duration from screening to completion.

### Key Study Endpoints and Assessments

The primary efficacy endpoint in all three studies is the percent change in calculated LDL-C from baseline to Week 24, using all LDL-C values regardless of adherence to treatment (intent-to-treat [ITT] approach). Key secondary endpoints are summarized in Table 2.

**Table 2 Tab2:** Primary and key secondary endpoints common to FH I, FH II and HIGH FH

Primary endpoint
% change in calculated LDL-C from baseline to Week 24 in the ITT population, using all LDL-C values regardless of adherence to treatment (ITT estimand)
Key secondary endpoints
% change in calculated LDL-C from baseline to Week 24 in the mITT population, using all LDL-C values during the efficacy treatment period (on-treatment estimand)
% change in LDL-C from baseline to Week 12 (ITT estimand)
% change in LDL-C from baseline to Week 12 (on-treatment estimand)
% change in Apo B from baseline to Week 24 (ITT estimand)
% change in Apo B from baseline to Week 24 (on-treatment estimand)
% change in non-HDL-C from baseline to Week 24 (ITT estimand)
% change in non-HDL-C from baseline to Week 24 (on-treatment estimand)
% change in total cholesterol from baseline to Week 24 (ITT estimand)
% change in Apo B from baseline to Week 12 (ITT estimand)
% change in non-HDL-C from baseline to Week 12 (ITT estimand)
% change in total cholesterol from baseline to Week 12 (ITT estimand)
% change in calculated LDL-C from baseline to Week 52 (ITT estimand)
Proportion of very high CV risk patients reaching calculated LDL-C <70 mg/dL (1.81 mmol/L) or high CV risk patients reaching calculated LDL-C <100 mg/dL (2.59 mmol/L) at Week 24 (ITT estimand)
Proportion of very high CV risk patients reaching calculated LDL-C < 70 mg/dL (1.81 mmol/L) or high CV risk patients reaching calculated LDL-C <100 mg/dL (2.59 mmol/L) at Week 24 (on-treatment estimand)
Proportion of patients reaching LDL-C <70 mg/dl (1.81 mmol/L) at Week 24 (ITT estimand)^a^
Proportion of patients reaching LDL-C <70 mg/dl (1.81 mmol/L) at Week 24 (on-treatment estimand)^a^
% change in Lp(a) from baseline to Week 24 (ITT estimand)
% change in HDL-C from baseline to Week 24 (ITT estimand)
% change in fasting TG from baseline to Week 24 (ITT estimand)
% change in Apo A1 from baseline to Week 24 (ITT estimand)
% change in Lp(a) from baseline to Week 12 (ITT estimand)
% change in HDL-C from baseline to Week 12 (ITT estimand)
% change in fasting TG from baseline to Week 12 (ITT estimand)
% change in Apo A1 from baseline to Week 12 (ITT estimand)

*Apo* apolipoprotein, *FH* familial hypercholesterolemia, *HDL-C* high-density lipoprotein cholesterol, *ITT* intent-to-treat, *LDL-C* low-density lipoprotein cholesterol, *Lp(a)* lipoprotein(a), *mITT* modified ITT, *TG* triglycerides

^a^Proportion of patients reaching LDL-C <70 mg/dL (ITT and on-treatment estimand) are the last key secondary endpoints for HIGH FH

In FH I, II and HIGH FH, LDL-C will be calculated using the Friedewald formula at screening and at all time points during the double-blind treatment periods. In FH I and II, if triglycerides exceed 400 mg/dL (4.52 mmol/L) then the central laboratory will reflexively measure LDL-C (via the beta quantification method) rather than calculating it. LDL-C will also be measured (via the beta quantification method) at Week 0 and Week 24.

On-site patient assessments take place at Weeks 0, 12, 24, 36, 52, 64, 78, and 86, the end-of-study visit. All laboratory tests are performed by the central laboratory.

Safety parameters (AEs [including adjudicated CV events categorized as CHD death, non-fatal MI, fatal and non-fatal ischemic stroke, unstable angina requiring hospitalization, congestive heart failure requiring hospitalization], laboratory data [blood biochemistry, hematology and urinalysis], vital signs and electrocardiogram) are assessed throughout the study.

### Statistical Design and Analysis

#### Sample Size Determination

In each study (FH I, FH II and HIGH FH), a total sample size of 45 patients (30 in the alirocumab and 15 in the placebo group) will have 95 % power to detect a difference in mean percent change in LDL-C of 30 % with a 0.05 two-sided significance level, assuming a common standard deviation of 25 % and all these 45 patients having an evaluable primary endpoint.

However, to meet regulatory requirements across the program, sample sizes were increased to assess the safety of alirocumab appropriately. Therefore, the final total sample sizes were increased and rounded to 471 in FH I, 250 in FH II and 105 in HIGH FH.

#### Analysis Populations for Each of the FH Studies

##### Primary Analysis

The primary analysis population will be the ITT population and will comprise all randomized patients with at least one baseline calculated LDL-C value available and at least one calculated LDL-C value available between Weeks 4 and 24 (regardless of treatment adherence). The percent change from baseline in LDL-C at Week 24 will be analyzed using a mixed effect model with repeated measures (MMRM) approach. All available post-baseline data from Week 4 to 24 (on- and off-treatment) will be used, in which missing data will be accounted for by the MMRM [28, 29]. The model includes fixed categorical effects of treatment group, randomization strata time point, treatment-by-time point and strata-by-time point interaction as well as the continuous fixed covariates of baseline LDL-C value and baseline value-by-time point interaction.

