##### Secondary Analysis

A hierarchical procedure will be used to control type I error and handle multiple secondary endpoints analyses. If the primary endpoint analysis (ITT) is significant at 5 % alpha level, key secondary efficacy endpoints will be tested sequentially in the order given in Table 2. In particular, LDL-C reduction at Week 24 will be analyzed on-treatment in the modified ITT population (i.e. patients with at least one baseline and at least one calculated LDL-C value available on-treatment between Week 4 and 24) if the primary analysis is significant in the ITT population.

Continuous secondary endpoints, except Lp(a) and triglycerides, will be analyzed using the same MMRM model as for the primary endpoint. Lp(a) and triglycerides (which have a non-Gaussian distribution), and the binary secondary endpoints (proportion of patients with LDL-C <70 mg/dL and <100 mg/dL) will be analyzed using a multiple imputation approach for handling of missing values followed by robust regression [30] (for Lp(a) and triglycerides) or logistic regression (for binary endpoints).

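### Optional precision gain: the MMRM adjusts for one baseline lipid value, although a screening value on the same stable therapy could be added for HDL-C, LDL-C, non-HDL-C and total cholesterol

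*Protocol article*

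**What the plan says.** Under Primary Analysis, the Week 24 percent change in LDL-C is analysed by an MMRM with treatment, randomization strata, time point and their interactions, "as well as the continuous fixed covariates of baseline LDL-C value and baseline value-by-time point interaction". No other pre-treatment lipid value enters. Under Secondary Analysis the model is carried over: "Continuous secondary endpoints, except Lp(a) and triglycerides, will be analyzed using the same MMRM model as for the primary endpoint". HDL-C, non-HDL-C and total cholesterol therefore get one pre-treatment value each.

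Three other places show that a second value is available.
- Key Study Endpoints and Assessments: "LDL-C will be calculated using the Friedewald formula at screening and at all time points during the double-blind treatment periods". Friedewald subtracts HDL-C and a fraction of triglycerides from total cholesterol, so all three are measured on the screening sample. Patients with screening triglycerides above 400 mg/dL are excluded, so the formula is usable at screening in those randomized.
- Study Procedures: screening lasts at most 3 weeks, and diet is to be stable from screening onward.
- Table 1: lipid-lowering therapy that is not stable is an exclusion, "as applicable, prior to the screening visit or from screening to randomization".

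The article does not define baseline as the Week 0 value or as an average of visits. It does not say that Apo B or Apo A1 is measured at screening.

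**The concern.** The endpoint is a percent change, so visit-to-visit error in the baseline value enters each patient's outcome through the denominator. Adjusting for that same value removes only part of this error. A second measurement taken shortly before, on the same therapy, shows how far the baseline value lies from the patient's usual level and can absorb more of it.

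The stake is precision, not validity. It matters most where power may be modest. The article sizes the trials on LDL-C and then enlarges them for safety. It gives no power for HDL-C, which sits late in a fixed sequence. In HIGH FH, eight tests follow the Week 24 HDL-C test and cannot be claimed if it fails: Week 24 triglycerides and Apo A1; Week 12 Lp(a), HDL-C, triglycerides and Apo A1; and the two proportions below 70 mg/dL, which the Table 2 footnote places last in that study.

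**Working it through.** **1. The plan's own figure.** Inputs from Sample Size Determination: "a total sample size of 45 patients (30 in the alirocumab and 15 in the placebo group) will have 95 % power" for "a difference in mean percent change in LDL-C of 30 % with a 0.05 two-sided significance level", "assuming a common standard deviation of 25" percent, with "all these 45 patients having an evaluable primary endpoint". The standard error is 25 × √(1/30 + 1/15) = 7.91, and 30/7.91 = 3.79. The two-sample t-test (noncentral t, 43 df) gives 96.0% power. At 42 patients it gives 94.7%, so 45 is the smallest 2:1 total reaching 95%. The figure is correct.

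**2. Primary endpoint at the actual sizes.** HIGH FH has 105 patients, or 70 and 35 at 2:1. The standard error is 25 × √(1/70 + 1/35) = 5.18, and 30/5.18 = 5.80, giving 99.99% power. FH II (250) and FH I (471) exceed 99.9999%.

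**3. Ceiling on the gain.** Let r be the correlation between any two visits, equal for all pairs, with no variation in response between patients. The residual variance with two pre-treatment values, divided by that with one, is (1 + 2r)/(1 + r)². At r = 0.5, 0.7, 0.8 and 0.9 the variance falls by 11%, 17%, 20% and 22%. As r approaches 1 the ratio approaches 3/4, so the variance can fall by at most 25% and the standard error by at most 1 − √0.75 = 13%. Variation in response between patients lowers the gain further.

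**4. Simulation at 70 vs 35.** Week 24 percent change was regressed on arm and the Week 0 value, with and without the screening value. This is a single-visit ANCOVA standing in for the MMRM, without strata or missing data. All variance inputs are assumptions, because the article gives only the 25% SD for LDL-C.

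HDL-C used between-patient SD 25%, true effect +7% and 8,000 replicates per setting. In one version the errors at the two pre-treatment visits are independent. In the other, 40% of the within-patient variance is common to both visits. Entries are the fall in standard error, then power without and with the screening value.

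| Within-patient CV | Response SD | Independent errors | 40% shared |
|---|---|---|---|
| 5% | 10% | 3.1%; 77.0 to 80.0% | 2.2%; 77.2 to 78.7% |
| 7% | 7% | 7.0%; 76.8 to 82.6% | 3.7%; 77.7 to 80.4% |
| 10% | 5% | 7.8%; 60.2 to 68.1% | 5.0%; 59.4 to 63.6% |
| 10% | 10% | 6.1%; 48.1 to 53.5% | 3.6%; 47.2 to 50.3% |

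Other runs with independent errors gave falls of about 4-9%. With no true effect (CV 7%, response SD 7%), both models rejected in 4.7-5.1% of replicates, so type I error is not affected.

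LDL-C used between-patient SD 30%, response SD 20%, within-patient CV 6-14%, screening value at least 160 mg/dL and effect −30%. The standard error fell by 0.8-2.2% with independent errors and 0.2-1.2% with 40% shared. Other assumed settings reached about 3%. Power was about 100% throughout.

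**5. Which study gains most power for HDL-C.** Assume SD 15% and a 15% cut in variance (noncentral t).

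| True difference | HIGH FH | FH II | FH I |
|---|---|---|---|
| 4 | 24.8 to 28.3% | 50.8 to 57.4% | 77.7 to 84.0% |
| 6 | 48.2 to 54.6% | 84.4 to 89.6% | 98.3 to 99.3% |
| 8 | 72.3 to 79.1% | 97.7 to 99.0% | about 100% |

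At a difference of 4 the gains are 3.5, 6.6 and 6.3 points, so HIGH FH gains least. At 6 and 8 it gains most (6.4 and 6.8 points).

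**The case against.** Adjusting for a single baseline value is conventional and valid, so nothing in the article is wrong or contradictory here. That stands, and it is why the point is only a suggestion.

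Baseline is also undefined. The ITT definition requires at least one baseline value, which leaves room for more than one. If the full protocol averages screening and Week 0, most of the gain is already taken. This stands as a condition on the advice.

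The HDL-C figures rest wholly on assumed inputs, and two visits at most 3 weeks apart may share short-term variation. This stands in part: sharing 40% of the within-patient variance roughly halves the gain but does not remove it. For LDL-C, screening is also the selection variable, which helps keep its gain small.

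Some stronger readings are tempting, and the documents do not support them.
- A reader might infer that the primary conclusion is at risk. It is not: power is already about 99.99% or more.
- A reader might infer that HIGH FH always benefits most. Its absolute standard error is the largest because it is the smallest study, but the power ranking changes with the true effect.
- A reader might extend the remedy to every secondary MMRM. No screening Apo B or Apo A1 is documented.
- A reader might conclude that the change secures the test sequence. Lp(a) immediately before HDL-C and triglycerides immediately after it use robust regression, and Apo A1 has no documented screening value. The sequence can still stop at any of these, and the chance of completing it has not been calculated.

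**Conclusion.** The point holds as an optional efficiency gain, provided baseline is the Week 0 value only. There is no bias, no type I error problem and no consequence for the primary result, whose standard error would shrink by about 0-3%.

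For HDL-C the standard error falls about 2-9% under assumed within-patient CVs of 5-10% and response SDs of 5-10%. In HIGH FH at an assumed +7% effect this is worth about 2-7 power points; single simulated settings ran from about 1.5 to 8. These are illustrations under stated assumptions, since the article gives no HDL-C variance, visit-to-visit correlation or expected effect.

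**What to change.** First state how baseline is derived. If it is the Week 0 value alone, add the screening value of the analysed parameter and its interaction with time point as continuous fixed covariates, next to the existing baseline terms. Do this for HDL-C, LDL-C, non-HDL-C and total cholesterol only. Keep percent change from baseline as the endpoint. If baseline already averages both visits, no change is needed.

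The wording must be fixed before unblinding, which means before the first-step analysis once Week 52 data are complete, because the key secondary results become final then. The cost is one sentence in the model specification and one extra covariate per time point, a small loss of degrees of freedom even with 105 patients. No new samples, visits or patients are needed.
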